### Study population

Study centres will be asked to identify eligible women of childbearing age (18–50 years) at the time of an early pregnancy attendance or at delivery who have had suspected COVID-19 or confirmed SARS-CoV-2 infection in pregnancy. Case data will be entered into the online registry. The study will recruit women affected by suspected COVID-19 or confirmed SARS-CoV-2 infection from January 2020 and March 2021. Participants will be able to withdraw from the register at any time without affecting their medical care. Participants should inform any member of the study team of their wish to withdraw consent. When a participant withdraws consent, they should be asked whether they are willing to allow ongoing data collection, such as maternal and fetal outcomes, from their medical records. If the participant withdraws consent and does not wish to have any further data collected, then this will be recorded on the database and no further data entry will be possible.

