### Sample size

Prespecified sample size estimation was not carried out given the aim of this observational study was to collate all consecutive eligible case outcomes in participating centres between data collection start and 18 months from start of data collection. It may be useful to provide an approximate guide as to the width of the 95% CI that can be achieved for proportions using historical data from the UK. These historical data may not hold during the current pandemic and may alter due to multiple reasons such as access to healthcare or behaviour changes. Contemporaneous data collected using other current national registries will provide true background rates for comparative purposes at the end of the study period. Generalising these data internationally may not be possible unless similar contemporaneous data exist for comparison.

The estimated representative pre-COVID pandemic incidences of miscarriage, Small for Gestational Age (SGA)/FGR and stillbirth in the UK were 30%, 10%, 0.2%, respectively. The expected outcome proportions during the COVID-19 pandemic are 40%, 15% and 0.4%, respectively. A sample size of 500 would allow the estimation of the width of 95% CIs for the proportion of miscarriage as 40%±4.2%, for SGA/FGR 15%±2.9% and for stillbirth 0.4%±0.3%.

These figures are meant only as a guide and reference proportions may change over this period. Since attaining sufficient precision for stillbirth requires by far the largest sample size, then study recruitment targets could be based on this rarest of outcomes. This would then provide sufficient precision to assess other more common outcomes. These figures are based on data from the UK only. Reference proportions vary by country but are of a similar order to those in the UK.

Appropriate quantitative analyses will be conducted by a study statistician. Dates collected from sites for expected data of delivery or last menstrual period, week of pregnancy at delivery and date of any COVID-19 tests in the participant or neonate will be cross-checked and validated for the final report. Regular interim reports will use contemporaneous data as it is collated.

Derived variables to be reported are:

Infection delivery interval (<2 or≥2 weeks after onset of suspected or confirmed COVID-19).Week of pregnancy when COVID-19 diagnosis was made.Number of days from delivery to SARS-COV-2 testBirth weight percentiles adjusted for gender and gestational age.

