Fortnightly bulletins will consist of counts of participants by country, proportions for maternal COVID-19 diagnosis status (suspected, positive test, negative test), week of pregnancy for COVID-19 diagnosis (<23 weeks, 23–36 weeks, ≥37 weeks), weeks of pregnancy at delivery (<23 weeks, 23–36 weeks, ≥37 weeks), maternal and neonatal mortality, outcome of delivery (live birth, miscarriage, intrauterine death, stillbirth (>22+6 weeks gestation)), FGR split by delivery interval (<2 vs ≥2 weeks), COVID-19 diagnosis status for babies split by number of days from delivery to test (0, 1–7, 8–28) and birth weight percentiles. Mean (SD) and median birth weights will also be reported. Further analysis will take place at one interim time point and at final data collection. For the interim analysis, a subset of validated outcomes will be reported consisting of total cohort proportions of gestation at delivery, birth weight Z-scores, perinatal mortality (stillbirth, early neonatal death), neonatal COVID-19 or SARS-COV-2 swab positive, neonatal morbidity and maternal death. These data will be split by suspected and confirmed COVID-19 diagnosis. Additional graphical exploratory analysis of the data will assess any possible association between the infection delivery interval and the timing of delivery as well as birth weight. The final analysis will report all demographic baseline data for the whole cohort and all outcomes as well as these graphical trends. Proportional data for the study outcomes will be presented with 95% CIs, by country, where numbers allow. Data and all appropriate documentation will be stored for a minimum of 10 years after the completion of the study, including the follow-up period.

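### Interim and bulletin proportions have no at-risk denominator although women may enter at delivery, and the guide precision at n=500 uses one denominator for three outcomes and gives only the lower interval arm

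*Protocol article*

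**What the plan says.** **Entry.** Under Study population, centres identify women "at the time of an early pregnancy attendance or at delivery who have had suspected COVID-19 or confirmed SARS-CoV-2 infection". Nothing limits the gestation at infection, and the bulletin bands for week of diagnosis run up to 37 weeks and beyond.

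**Denominators.** The analysis text stands at the end of the Sample size section.
- For the single interim analysis, "a subset of validated outcomes will be reported consisting of total cohort proportions of gestation at delivery", together with birth weight Z-scores, perinatal mortality, neonatal swab positivity, neonatal morbidity and maternal death. Miscarriage is not in that list.
- The fortnightly bulletins give pregnancy outcome as one distribution (live birth, miscarriage, intrauterine death, stillbirth). They give gestation at delivery as another. Stillbirth is defined as after 22+6 weeks. Week of diagnosis is tabulated but is not said to be crossed with outcome.
- "The final analysis will report all demographic baseline data for the whole cohort and all outcomes as well as these graphical trends". Outcome proportions then get 95% CIs by country, and no denominator is named.

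**Comparison.** "Contemporaneous data collected using other current national registries will provide true background rates for comparative purposes" at the end of the study.

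**Precision.** No formal sample size was set. The section offers "an approximate guide as to the width of the 95% CI that can be achieved for proportions". It assumes that "The expected outcome proportions during the COVID-19 pandemic are 40%, 15% and 0.4%, respectively" for miscarriage, SGA/FGR and stillbirth. It then takes one n of 500 for all three outcomes and states the precision "for the proportion of miscarriage as 40%±4.2%, for SGA/FGR 15%±2.9% and for stillbirth 0.4%±0.3"%. The figures are called a guide, but the text adds that recruitment targets could be based on stillbirth.

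**The concern.** The principal question is the incidence of miscarriage, SGA/FGR and stillbirth, preterm birth and vertical transmission in registered women. An incidence needs a denominator of women who could still have the event when they came under observation. By the protocol's own cut-points, infection at 23 weeks or later cannot be followed by a miscarriage, and infection at 37 weeks or later cannot be followed by a preterm birth. A woman first identified at delivery has, by construction, already passed the risk period for miscarriage.

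Two forces act on a proportion that ignores this. Late entry adds women who were never at risk and so dilutes it. Easier identification of women who attend because of a loss inflates it. The result reflects who was registered and when, as well as the risk. National background rates do not share that mix, so the planned comparison could mislead, and the article intends its reports to reach policymakers quickly.

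The guide precision has the same denominator problem. A pregnancy that ends in miscarriage cannot also yield a stillbirth after 22+6 weeks or a birth weight for an SGA assessment, yet one figure of 500 is used for all three.

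**Working it through.** **1. The plan's own half-widths.** Inputs from the Sample size section: n = 500, 95% level, p = 0.40, 0.15 and 0.004.

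Wald: h = 1.96 × √(p(1−p)/n).
- Miscarriage: 1.96 × √(0.40 × 0.60/500) = 4.29 points
- SGA/FGR: 1.96 × √(0.15 × 0.85/500) = 3.13 points
- Stillbirth: 1.96 × √(0.004 × 0.996/500) = 0.55 points

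These do not reproduce the stated 4.2, 2.9 and 0.3.

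Wilson, with k = 1.96: centre (p + k²/2n)/(1 + k²/n), half-width [k/(1 + k²/n)] × √(p(1−p)/n + k²/4n²).

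| Outcome | Stated ± | Wilson 95% | Lower arm | Upper arm |
|---|---|---|---|---|
| Miscarriage 40% | 4.2 | 35.8–44.4% | 4.20 | 4.35 |
| SGA/FGR 15% | 2.9 | 12.1–18.4% | 2.86 | 3.40 |
| Stillbirth 0.4% | 0.3 | 0.11–1.45% | 0.29 | 1.05 |

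All three stated values equal the lower Wilson arm, printed as if it were symmetric. This matters little for miscarriage and a great deal for stillbirth. A Wald half-width of 0.3 points would need 0.004 × 0.996 × (1.96/0.003)² ≈ 1,701 pregnancies.

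**2. One n for three outcomes.** If 40% of 500 miscarry, as the plan expects, at most 500 × 0.60 = 300 pregnancies remain.
- SGA/FGR: 1.96 × √(0.1275/300) = ±4.0 points (Wilson 11.4–19.5%)
- Stillbirth: 1.96 × √(0.003984/300) = ±0.71 points (Wilson 0.08–1.97%)
- Expected stillbirths: 300 × 0.004 = 1.2; chance of none: 0.996³⁰⁰ = 30%

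The step from the stated 0.3 to 0.71 has two parts: 0.25 points from the interval error (0.3 to 0.55) and 0.16 from the denominator (0.55 to 0.71).

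**3. Dilution of miscarriage.** *Assumption:* a share f of 500 women is infected while at risk, and those women carry the full 40% risk. The documents do not give f. Total-cohort proportion = 0.40f; at-risk half-width = 1.96 × √(0.24/(500f)).

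| f | Total-cohort proportion | At-risk 95% half-width |
|---|---|---|
| 10% | 4% | ±13.6 |
| 20% | 8% | ±9.6 |
| 30% | 12% | ±7.8 |
| 50% | 20% | ±6.1 |
| 75% | 30% | ±5.0 |

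At f = 75% the expected 40% appears as 30%, the plan's own pre-pandemic figure.

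**4. Dilution of preterm birth.** *Assumption:* a risk of 22% in women at risk, borrowed for illustration from the 94 of 428 babies in the review cited in the Introduction. If 10%, 30% or 50% of women are infected at 37 weeks or later, the total-cohort proportion is 0.22 × 0.90 = 19.8%, 0.22 × 0.70 = 15.4% or 0.22 × 0.50 = 11.0%.

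**5. Bias the other way.** *Assumption:* a true miscarriage risk of 30%, all losses captured, continuing pregnancies half as likely to be captured. The observed proportion is 0.30/(0.30 + 0.70 × 0.5) = 46%.

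**6. Why subgrouping alone is not enough.** A woman infected at, say, 18 weeks is still at risk of miscarriage but has already survived the earlier weeks. Counting her as exposed to the whole risk period understates the risk. She should contribute only from the gestation at which she enters.

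**The case against.** **The interim sentence is narrow.** It covers one analysis and omits miscarriage. A reader might infer that the total cohort is fixed as the denominator for miscarriage and for the final analysis. The text does not say so: the final denominator is simply unstated, and the whole-cohort phrase there attaches to baseline data. This objection stands. What remains is the preterm distribution at the interim analysis and the bulletins' single outcome distribution, which does include miscarriage.

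**Total cohort may only mean before the split by suspected and confirmed diagnosis.** This is plausible, since several listed items exist only for births. But that reading supplies no at-risk denominator either.

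**Analysis sets may be in a SAP or full protocol that is not shown.** Fair, and silence about the final denominator is not by itself a fault. The data allow restriction: the date fields are collected, and the diagnosis bands use the same 23 and 37 week cut-points. But the article does fix some displays without that restriction, and the numerical precision statement is wrong wherever the details sit.

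**The aim is descriptive.** It concerns women recruited to the registry, and the limitations admit incomplete capture. They do not mention entry after the risk period, and the planned comparison with background rates invites a reading as risk.

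**The n = 300 and dilution arguments belong to different scenarios.** Correct. If only 4% to 20% of 500 miscarry, 480 to 400 pregnancies remain. SGA/FGR is then ±3.2 to ±3.5 points and stillbirth ±0.56 to ±0.62. The figure of 300 applies only on the plan's own 40%.

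**The 500 is only a guide.** True. It also covers three outcomes, not every one: no precision is given for preterm birth or vertical transmission. A guide should still be right, because it may inform recruitment targets.

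**Conclusion.** The point holds in limited form. The interim preterm proportions and the bulletin outcome distribution, as written, mix in women who could not have the event after infection. They can be seriously biased. Neither the size nor the direction can be derived from the documents, because the distribution of gestation at infection and at registration is not given. The range of 4% to 20% for a true 40% miscarriage risk rests on the assumption that 10% to 50% of women were infected while at risk. A reader might go further and conclude that the incidences will certainly be too low, or that harm will look protective. Selective capture of losses could push the other way, so the documents do not support that.

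The precision error needs no such assumption. The stated ± values are lower Wilson arms, and for stillbirth the upper arm is more than three times as long (1.05 against 0.29 points). On the plan's own 40%, the shared n = 500 also overstates the pregnancies available for SGA/FGR and stillbirth by at least 200.

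**What to change.** 1. Replace total-cohort proportions with a named denominator for each outcome:
   - miscarriage: women infected and registered before 23+0 weeks;
   - preterm birth: births at or after 23+0 to women infected before 37+0;
   - stillbirth and SGA/FGR: births at or after 23+0;
   - neonatal death: live births.
2. For miscarriage and preterm birth, analyse on the gestational-age scale with delayed entry (Kaplan-Meier or Aalen-Johansen), entering at the later of infection and registration.
3. Report women whose outcome was already known at registration separately.
4. Compare with background risks conditional on the same starting gestation.
5. Restate the guide precision as asymmetric intervals, each on its own denominator. At n = 500 they are 35.8–44.4%, 12.1–18.4% and 0.11–1.45%; on the smaller correct denominators they are wider.
6. Keep the present whole-cohort displays as a secondary table, labelled as descriptive of the registry.

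**Cost.** The change is mainly in wording. Last menstrual period, expected delivery date, test dates and delivery dates are already collected; the registration date is also needed. The real cost is precision. Women first identified at delivery or at a completed loss add no time at risk, so the miscarriage and preterm estimates may rest on many fewer women and their intervals will widen.

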## Ethics and dissemination

The Study Coordination Centre has obtained approval from the Haydock Research Ethics Committee (REC) and Health Regulator Authority, REC reference: 20/NW/0212 and had been considered to be an Urgent Public Health study by the UK Clinical Research Network.

The study must also receive confirmation of capacity and capability from each participating NHS Trusts in the UK before accepting participants into the study or any research activity is carried out. The study will be conducted in accordance with the recommendations for physicians involved in research on human subjects adopted by the 18th World Medical Assembly, Helsinki 1964 and later revisions. The international participating centres will be required to obtain appropriate local approval from their centres. All those taking consents will be qualified and trained to take consent in a medical context. To reduce face-to-face consultations during the pandemic verbal consent will be obtained after provision of the participant information sheet: Patient Information Sheet (PIS) (online supplemental appendix 1), which will have details of how to contact the PAN-COVID study team, if they would like further information or to withdraw from the study and this will be recorded in the patients notes and on the study database. Where women have lost capacity to provide consent and have confirmed COVID-19, women will be assumed to provide consent. If they regained capacity, the study will be explained to them and they will be provided with the PIS, which will have details of how to contact the PAN-COVID study team, if they would like further information or to withdraw from the study. If they choose to withdraw, data pertaining to their care would be removed from the registry. Where feasible, the woman’s partner or a family member will be provided with the PIS and asked if they feel able to advise on the presumed wishes and feelings of participants unable to consent for themselves and on their inclusion in the research. Their response will be recorded on the database and in the participants’ clinical notes. These models will give a reasonable opportunity for women to provide their data to the study, while being mindful not to over burden healthcare resources. Research has shown that within a pandemic, potential participants and their families are broadly agreeable to alternative methods of gaining consent, therefore we decided on this verbal model of consent, as a pragmatic solution to ensure women are informed of how their data will be used and alleviate additional burden to healthcare resources.^16^ The chief investigators (CL and EM) will preserve the confidentiality of participants taking part in the study and is registered under the General Data Protection Regulation (GDPR) 2018. In terms of indemnity, Imperial College London holds negligent harm and non-negligent harm insurance policies that apply to this study. Imperial College London will act as the Sponsor for this study. Delegated responsibilities will be assigned to the NHS trusts taking part in this study. The study may be subjected to inspection and audit by Imperial College London under their remit as sponsor and other regulatory bodies to ensure adherence to Good Clinical Practice (GCP) and the UK Policy Framework for Health and Social Care Research.

10.1136/bmjopen-2020-041247.supp1Supplementary data

### Data security

Cardiff University has strict policies and processes in place to ensure adherence to the GDPR^2^ The University is registered on the Information Commissioner’s Office Data Protection register, number Z6549747. All data collected on the Registry will be held on Cardiff University servers, which have a high level of security. CTR database developers have run a security check on the trials.cardiff.ac.uk server and it has passed to an acceptable standard to EU and non-EU centres.

The person allocating centre IDs and logins will not have access to the database fields containing personal information. For healthcare professionals to enter follow-up data, they will need to maintain a secure spreadsheet (password protected) with participants’ identifiable information logged against their unique participant identification number.

To reduce any potential risk of identification of study participants, access will be restricted to the section of the database containing identifiable information (NHS number, date of birth, ethnicity) to those responsible for maintaining the database (two individuals). This will mean that the CTR members of the research team (two different individuals) responsible for allocating the unique centre and participant IDs will not be able to access any identifiable data. In addition, all other CTR members of the research team will be blinded to which centre ID relates to which centre. For statistical analyses, a data set will be prepared by the database developers which will have all NHS numbers, and the international equivalent, removed, reducing possible identification of participants further.

### Patient and public involvement

Patients and public were not involved in the initial research idea and study design, due to the rapid response required at the start of the COVID-19 pandemic and lockdown. The NIHR funded this research and involves patients and public in setting research priorities and in reviewing funding applications. Patients and the public will be notified of the results through our established links within the UK including the Royal College of Obstetrics and Gynaecology (RCOG), International Society of Ultrasound in Obstetrics and Gynaecology (ISUOG), International Federation of Gynaecology and Obstetrics (FIGO) and related partner charities and with our US partner the AAP. We expect that the major publications from this study will be widely cited in the scientific and lay press and this will prove to be the most effective route of dissemination.

### Dissemination

Regular reports of case data will be made available on the study website. Although members of the public were not involved in the study design as it is broadly a registry, the maternity and neonatal focus groups will be involved in the dissemination of the outputs. The outputs of the PAN-COVID registry will be presented in national and international conferences, lay and digital social media and published in peer-reviewed scientific journals which will be made available as open access, as per the NIHR’s publication policy.
